2.1　Rationale for conducting clinical trials

The dose of ethanolamine oleate administered in this study is within range the previously approved for gastric varices. In addition, no problematic events have been reported for venous malformations at that dosage that differ from the known profile in the previously approved indication, and efficacy has already been reported in multiple literature reports, so we believe that additional nonclinical studies are unnecessary. Many of the clinical studies reported to date however, have subjective endpoints and therefore evidence on efficacy is limited. Therefore, we believe that it is necessary to conduct a clinical trial to objectively validate treatment efficacy.

2.2　Purpose of the clinical trial

The purpose of this study is to evaluate the efficacy and safety of sclerotherapy in patients with difficult-to-resect venous malformations when treated with monoethanolamine oleate.

2.3　Risk/benefit

All subjects participating in this clinical trial are patients with difficult-to-resect venous malformations that will directly benefit from receiving a therapeutic agent for venous malformations, as there is currently no effective treatment for these lesions. An improvement in quality of life (QOL), such as relief of pain associated with venous malformations, is particularly expected.

All subjects participating in this clinical trial will receive the general medical benefit of careful and close observation by a health care professional during their participation in the clinical trial. Subject safety will be ensured through monitoring of adverse events based on clinical symptoms and laboratory tests. If the investigator or sub-investigator determines that there is a clinical concern, the safety of the subject will be given top priority.

In clinical studies of ethanolamine oleate for venous malformations, tenderness and swelling at the injection site are known to be typical side effects. Choi et al. reported local tenderness and swelling in all patients.^8)^ Other side effects include hemoglobinuria in 41.3-42.9%^9, 10)^, ulceration and skin necrosis in 3.0-14.7%^9-12)^, dysphagia in 7.7-12.5% of lesions adjacent to the buccal masseter muscle, and laryngeal edema in one case. Therefore, blood and urine tests should be performed the day after administration, and if hemoglobinuria or renal function deterioration is observed, these risks should be explained to the subject or surrogate.

Summary of Animal Experiments

Single-dose toxicity:

In rats, the fatal cases showed symptoms such as open mouth breathing, chain-stokes-like breathing, and clonic convulsions, and most of the deaths were due to respiratory paralysis. In dogs, urinary incontinence, tonic convulsions, and death occurred after respiratory distress.

Repeated dose toxicity:

A 4-week intravenous toxicity study in dogs was conducted at doses of 93, 31, 10, and 3 mg/kg every other day for 4 weeks (continuous administration was not possible due to site of administration swelling and hardening). No deaths occurred during the treatment period, but hematuria was observed in all groups, increased fibrinogen levels in the group of 31 mg/kg or higher, and decreased red blood cell counts, hematocrit and hemoglobin levels, increased white blood cell counts, and increased total bilirubin in the 93 mg/kg group. Pathological examination revealed thrombus formation and thickening of the vessel wall at the site of administration and granulosa cell infiltration of the dermis in the 3 mg/kg group and above, erythroblastic hyperplasia of the bone marrow and brown pigmentation of the renal tubular epithelium in the 31 mg/kg group and above, and thymic cortex atrophy and thrombus formation in the liver in the 93 mg/kg group. Based on the above, the toxicologically no-effect dose of the drug was estimated to be 10 mg/kg and the reliably toxic dose to be 93 mg/kg.

Antigenicity:

Results of systemic anaphylactic shock, PCA reaction test, and Schulzdale reaction test in guinea pigs were all negative.

Mutagenicity:

No mutagenicity was observed in reversion mutagenicity tests using bacteria (Salmonella, Escherichia coli) and mutagenicity tests using mammalian cultured cells by chromosome aberration tests.

Local disability:

　Local toxicity studies were performed in rabbits by intramuscular administration at doses of 5% and 0.05% concentration (1 mL). Gross findings showed mild white changes in all patients in the 0.05% group and moderate or greater white changes and mild to moderate hyperemia, hemorrhage, brownish changes, and swelling in all patients in the 5% group on day 2 after administration. On day 7 post-dose, there were no changes in the 0.05% group and mild to moderate white changes, swelling, and intense browning in all patients in the 5% group. Histological examination revealed dose-dependent edema of the hemorrhagic stroma, changes and necrosis of muscle fibers, and infiltration of histiocytes in both groups on post-dose day 2, as well as tumor and multinuclear cell infiltration in the 5% dose group. On day 7 after treatment, the above changes disappeared in the 0.05% group, and calcification of myofibers, fibroblast proliferation, and fibrosis were mildly observed. In the 5% treatment group, changes in hemorrhage myofibers, calcification, myoblast proliferation, fibrosis, moderate necrosis of myofibers, and fibroblast proliferation were observed.

3. Study design and study subjects population

3.1　Overall design and plan of the study

This is an open-label, multicenter, single-arm study to evaluate the efficacy and safety of monoethanolamine oleate (upper limit of 0.4 mL/kg as 5% monoethanolamine oleate) in difficult-to-resect venous malformations.

Subjects will be included in the study after written consent is obtained from the subject or surrogate. If screened and found eligible, the subject will be enrolled and administered monoethanolamine oleate. The observation period will be 3 months, and an efficacy test will be conducted after 3 months of treatment. If additional treatment (one time) is given, the efficacy evaluation will be conducted 3 months after the additional administration.

Termination of the study is defined as the date of last observation for the subject as a whole.

The overall clinical trial design is shown in Figure 3.1-1.

[Basis for setting up].

Because the difficult-to-resect venous malformations that are the subject of this study basically worsen without treatment, it is ethically difficult to establish a placebo group. Therefore, this clinical trial was an open-label, single-arm study in which only the actual drug group was administered. For the rationale for setting the target number of patients, see "8.6.2 Rationale for Setting the Target Number of Patients.

**
[figure not shown]
**

[figure not shown]

Figure 3. 1-1 Clinical trial design

3.2　Selection of the study population

3.2.1　Name of disease or diagnosis covered by this clinical trial

This clinical trial will be conducted in patients diagnosed with difficult-to-resect venous malformations.

3.2.2　Eligibility criteria

Patients who meet all of the following the inclusion criteria and do not violate any of the exclusion criteria will be eligible

3.2.2.1　Inclusion criteria

1. No age limitation
2. Signed informed consent from patient or legal guardian(s) (In case age of patient is under 20 years old)
3. Venous malformations are considered difficult to remove, and sclerotherapy is considered first line treatment option by investigator/subinvestigator. Difficulty to remove means a high risk of functional dysfunction due to excision, or a loss of appearance to affect in daily life.
4. Patients who have one or more target venous malformations with a major axis of 30 mm or more in extremities, and 20 mm or more in head and neck region on MRI or CT
5. No thrombus and organized tissue that affects image evaluation or effect judgment in target venous malformations

*: For patients 5 years of age or younger, the Clinical Trial Coordinating Committee will evaluate the appropriateness of inclusion or exclusion in advance.

3.2.2.2　Exclusion criteria

1. Patients with multiple organ failure or DIC (Disseminated intravascular coagulation)
2. Patients who are taking or have taken drugs that may affect resolution of lesions (propranolol, herbal medicines [such as Kamishoyosan, Ninjinyoeito, Eppikajutsuto or Ogikenchuto], or sirolimus). However, patients can participate in the clinical study in case herbal medicines are discontinued 2 weeks or more before study drug administration.
3. Patients with diabetes mellitus with HbA1c>=8.0, or autoimmune disorder
4. Patients with hepatic dysfunction grade C (10-15 points) in Child-Pugh classification
5. Patients with renal dysfunction with eGFR < 60mL/min/1.73m2
6. Patients with cardiac dysfunction with over grade II in NYHA classification
7. Patients who received sclerotherapy within 6 months before obtaining informed consent
8. Patients with history of allergy to ethanolamine oleate or angiographic X-ray contrast agent as concomitant drugs
9. Patients who have undergone surgery longer than 45 minutes within 2 weeks before obtaining informed consent
10. Patients participating in other clinical study within 4 weeks before obtaining informed consent
11. Pregnant women, women who may be pregnant, or lactating women
12. Patients who are judged as inappropriate by investigator/subinvestigator

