3.2.2.3　Basis for establishing inclusion and exclusion criteria

Inclusion criteria

1: The target age for this clinical trial is not specified.

However, data collection for pain and QOL assessment will not be mandatory for patients aged 5 years or younger at the time of consent, as it is considered difficult to assess pain and QOL, which are part of the secondary endpoints. In the case of patients under 5 years of age, the Coordinating Committee will evaluate the appropriateness of inclusion or exclusion in advance.

4: In the field of plastic surgery in Japan, the size classification for tumor resection covered by insurance is 20 mm for the head and neck region and 30 mm for the extremities and trunk, and the same classification is used in actual clinical practice. In addition, the size at which detailed evaluation of venous malformation volume reduction or regression is possible on MRI is 20 mm or larger. Therefore, we judged it appropriate to set the target lesion size at 30 mm or larger in long diameter for the extremities and trunk and 20 mm or larger in long diameter for the head and neck.

2, 3: To select subjects who meet the objectives of the study, as well as to comply with GCP and ensure the safety of the subjects

5: Because it is difficult to evaluate images and determine effectiveness of treatment.

Exclusion criteria

1-7, 9-12: To take into account the safety of the subjects and to eliminate unexpected influences on the study results

8: To ensure the safety of the subject. However, when performing sclerotherapy for venous malformations, it is necessary to prepare the drug with an angiographic X-ray contrast medium. Therefore, if the patient is allergic to a specific contrast medium, it is necessary to select a different contrast medium that is usable (does not cause allergy) for the patient. The measures above are considered acceptable from a risk-benefit perspective since the subject is a patient who has no treatment options and whose ADL has declined due to pain and other symptoms deriving from the lesion.

4. Treatment

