5.1.1　Primary endpoint

Achievement of at least 20% reduction in volume of venous malformations from baseline (prior to administration) at 3 months of treatment with the investigational drug

[Basis for setting up].

Validity of the evaluation items:

In an ongoing Japanese investigator-initiated clinical trial of oral sirolimus treatment for lymphatic malformations, which is a similar disease of venous malformations, a 20% or greater reduction in the volume of the target lesion on MRI is considered a partial response (PR). Since the presence of a lesion can cause various symptoms, a reduction in volume of 20% or more is clinically significant. In addition, many literature studies have shown that patients with lesion reduction also experience improvement in pain.

In a trial conducted in the U.S. for oral sirolimus treatment of refractory vascular malformations, one of the endpoints was a 20% or greater reduction in the volume of the target lesion by MRI as PR, and the above domestic trial is based on this evaluation standard.

Validity of the evaluation period:

In evaluating the efficacy of sclerotherapy with monoethanolamine oleate, previous reports include Kaji et al.^5)^ evaluated by MRI at 3 months after treatment; Hoque et al.^6)^ evaluated at 8 weeks after sclerotherapy. A trial of gastric varices with a similar mechanism evaluated at 90 days after treatment. Based on these previous reports, the evaluation period was set at 3 months.

Regarding safety, Nomura et al. reported^9)^ that skin necrosis or mucous membrane necrosis was observed in 14.7% of patients, but all of them improved with conservative treatment. The average time required for healing was 58.6 days (maximum approximately 90 days). Generally, the adverse drug reactions by sclerotherapy occur within a few days of treatment, and considering the period until the adverse drug reactions are cured as the necessary observation period, it is reasonable to set the evaluation period at 3 months.

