5) Including photograph of the lesion site while observing the appearance.

6) Based on the patient's body weight on the day before dosing, a maximum dose of 0.4 mL/kg of 5% monoethanolamine oleate should be administered as the extreme dose (maximum is 30 mL).

7) The volume of blood collected is approximately 11 mL (maximum volume). The laboratory tests performed are red blood cell count, hemoglobin, hematocrit, white blood cell count, platelet count, white blood cell fraction (neutrophils, lymphocytes, eosinophils, basophils, monocytes), PT, APTT, PT-INR, fibrinogen, antithrombin III, FDP, D-dimer, Na, K, Cl, Ca, IP, BUN, Cre, UA, AST, ALT, LDH, γ-GTP, T.Bil, TP, Alb, ALP, CK, TG, T-chol, HDL-chol, AMY, CRP, Glu

8) Any laboratory data (within 30 days prior to obtaining consent) performed in the clinical setting unrelated to this study may be adopted as pre-dose data. However, for MRI, as a general rule, this shall be the case when imaging conditions specified in the "Imaging Evaluation Procedures" are used. In addition, if consent is obtained again for some reason, it is acceptable to use the MRI data as preadministration data if the initial MRI images were taken within 90 days from the date of consent.

9) If clinically relevant abnormalities are observed in clinical laboratory tests (blood) and urinalysis, such tests should also be performed 3 days after administration.

10) Urinalysis items (qualitative) are sugar, protein, urobilinogen, occult blood, leukocytes, pH, and specific gravity.

11) For pain rating scales, VAS is used for patients 6 years of age and older; Face scale is used for patients 2 to 5 years of age, however, evaluation for this group is not mandatory. For guardians, VAS is used if the patient is 6 to 14 years old, and Face scale is used if the patient is 5 years old or younger to evaluate from the guardian’s perspective. (The evaluation scale is shown in Appendix 2.)

For patients

| Patient Age | | 0 year old | 1 year old | 2-4 years old | 5 years old | 6-7 years old | 8-12 years old | 13-14 years old | 15 years and older |
| --- | --- | --- | --- | --- | --- | --- | --- | --- | --- |
| pain | VAS |  |  |  |  | X | X | X | X |
|  | Face scale |  |  | X* | X* |  |  |  |  |

*: Evaluation is not mandatory.

For guardians

| Patient Age | | 0 year old | 1 year old | 2-4 years old | 5 years old | 6-7 years old | 8-12 years old | 13-14 years old | 15 years and older |
| --- | --- | --- | --- | --- | --- | --- | --- | --- | --- |

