6.2.1　Before administration (screening)

After obtaining consent from the subject or surrogate, the subject's eligibility for participation in this clinical trial will be determined through screening observations and examinations in accordance with "3.2.2 Eligibility criteria".

With regard to "clinical examination," "urinalysis," and "MRI (when imaging is performed under the imaging conditions of the Imaging Evaluation Procedures)," if there are observation and examination results obtained within one month (30 days) prior to obtaining consent, they may be adopted as screening data after obtaining consent from the subject or surrogate. In addition, if consent is obtained again for some reason, it is acceptable to adopt the MRI images initially taken as screening data if they were obtained within 90 days from the date of re-consent.

If determined to be eligible, the subject will be enrolled.

The following observations and examinations will be performed.

1. Appearance (also take photographs of the lesion site)
2. Laboratory tests (red blood cell count, hemoglobin, hematocrit, white blood cell count, platelet count, white blood cell fraction [neutrophils, lymphocytes, eosinophils, basophils, monocytes], PT, APTT, PT-INR, fibrinogen, antithrombin III, FDP, D-dimer, Na, K, Cl, Ca, IP, BUN, Cre, UA, AST, ALT, LDH, γ-GTP, T.Bil, TP, Alb, ALP, CK, TG, T-chol, HDL-chol, AMY, CRP, Glu)
3. Urinalysis (urine qualitative: sugar, protein, urobilinogen, occult blood, white blood cells, pH, specific gravity)
4. Subjective symptoms (pain)
5. MRI (CT and ultrasound examination, if necessary)
6. QOL (including ADL)
7. Adverse event
8. Concomitant medications

6.2.2　1 day before administration

The following observations and examinations will be performed on the day before sclerotherapy (administration of the study drug). The subject should be hospitalized.

1. Vital signs (blood pressure, pulse rate, body temperature, SpO_2_)
2. Body weight
3. Subjective symptoms (pain)
4. Adverse event
5. Concomitant medications

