6.2.3　Treatment period

6.2.3.1　Date of administration

The investigational drug will be administered within 1 month (within 30 days) after obtaining consent from the subject or the surrogate.
 If the drug is not administered after one month from obtaining consent, re-consent will be obtained to confirm the subject's or surrogate's willingness. The subject should be managed as an inpatient.

The following observations and examinations will be performed.

(1) Administration of investigational drug

At each site, the investigational drug is received from the investigational drug manager.

Based on body weight on the day prior to administration, administer the investigational drug at a maximum dose of 0.4 mL/kg of 5% ethanolamine oleate (extreme dose is 30 mL). The dose (mL) administered should also be recorded.

(2) Adverse events

(3) Concomitant medications

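### The herbal-medicine stop is timed from dosing but the primary endpoint is measured from an earlier baseline MRI, so permitted herbal exposure can fall inside the measured interval

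*Protocol*

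**What the plan says.** All references are to the protocol.

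- **Premise.** Criterion 2 in 3.2.2.2 excludes "Patients who are taking or have taken drugs that may affect resolution of lesions", and its list includes herbal medicines. Section 3.2.2.3 gives part of the reason for this group of criteria as "to eliminate unexpected influences on the study results".
- **Exception.** The same criterion then says that "patients can participate in the clinical study in case herbal medicines are discontinued 2 weeks or more before study drug administration". The reference point is dosing.
- **On-study ban.** Section 4.2.1 prohibits the same classes of drug from the day of administration to the end of observation, so that the effect of the study drug can be evaluated properly. It does not reach back to screening.
- **Endpoint.** Section 5.1.1 defines it as "Achievement of at least 20% reduction in volume of venous malformations from baseline (prior to administration) at 3 months of treatment". The only scheduled pre-dose MRI is the screening one (Tables 6.1.1-1 and 6.1.2-1).
- **Age of the baseline MRI.** Section 6.2.1 allows earlier clinical data: "if there are observation and examination results obtained within one month (30 days) prior to obtaining consent, they may be adopted as screening data". After re-consent the first MRI may still be used "if they were obtained within 90 days from the date of re-consent". Footnote 8 to Table 6.1.1-1, and likewise footnote 10 to Table 6.1.2-1, words the limit differently: "if the initial MRI images were taken within 90 days from the date of consent".
- **Consent to dosing.** Section 6.2.3.1: "The investigational drug will be administered within 1 month (within 30 days) after obtaining consent".
- **Recording.** Section 4.2 has concomitant medication recorded from consent onwards.

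**The concern.** The protocol regards these medicines as a possible influence on the lesion and controls them after dosing. The endpoint, however, does not start at dosing. It starts at the baseline image. The stretch from that image to 14 days before dosing lies inside the measured interval, but outside both the washout and the ban.

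There is no control arm against which change in that stretch could be set. Whatever happens to the lesion there becomes part of the reduction attributed to ethanolamine oleate. The per-protocol set does not remove such a subject, because it drops violations of the criteria and significant deviations, and this subject has followed the rules. If the baseline MRI predates consent, herbal use between that MRI and consent is also outside the recording period in 4.2. A later sensitivity analysis might then be unable to identify the subjects concerned.

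**Working it through.** **1. The plan's own figure.** Section 8.6.2.1 gives 19 cystic cases for 80% power, with a null rate of 20%, an expected rate of 50% and a one-sided 2.5% exact binomial test.

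- n = 19, success at 8 or more: P(X ≥ 8 | 0.20) = 0.0233; P(X ≥ 8 | 0.50) = 0.820.
- n = 18, success at 8 or more: power 0.760, which is too low.

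So 19 reproduces. At the target of 22 (success at 9 or more), alpha is 0.0201 and power 0.857. Nothing below alters these figures.

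**2. Permitted herbal exposure after the baseline MRI.** Inputs: MRI up to 30 days before consent, or 90 days before re-consent (6.2.1); dosing up to 30 days after consent (6.2.3.1), with the re-consent taken as restarting that window; stop at least 14 days before dosing (criterion 2).

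Maximum exposure = (MRI to consent) + (consent to dosing) − 14.

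| Path | MRI to dosing, days | Herbal exposure after MRI, days |
|---|---|---|
| MRI on the day of consent | 0 + 30 = 30 | 30 − 14 = 16 |
| MRI before consent | 30 + 30 = 60 | 60 − 14 = 46 |
| Re-consent, first MRI reused | 90 + 30 = 120 | 120 − 14 = 106 |

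Each row combines the oldest permitted MRI for that path, the latest permitted dosing and the shortest permitted stop. They are upper limits. The post-dose period to the endpoint is 12 weeks, or 84 days, so the re-consent maximum is longer than it.

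**3. What that could do to the test (illustration only).** Let f be the share of subjects with such exposure and q the share of them whose responder status it changes. The protocol gives neither, so both are assumed. Take n = 22 with success at 9 or more.

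- *Inflating case:* the true sclerotherapy response is at the 20% null, and continued shrinkage turns a share q of would-be non-responders into responders. Observed rate = 0.20 + 0.80fq.
- *Deflating case:* the true response is 50%, and regrowth turns a share q of would-be responders into non-responders. Observed rate = 0.50 − 0.50fq.

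| f | q | Inflated rate | Chance of a false positive | Deflated rate | Power |
|---|---|---|---|---|---|
| 0 | 0 | 0.200 | 0.020 | 0.500 | 0.857 |
| 10% | 10% | 0.208 | 0.026 | 0.495 | 0.846 |
| 10% | 25% | 0.220 | 0.036 | 0.4875 | 0.829 |
| 20% | 25% | 0.240 | 0.060 | 0.475 | 0.797 |
| 20% | 50% | 0.280 | 0.134 | 0.450 | 0.724 |

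The effect runs from negligible to serious depending on quantities that the protocol does not supply.

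**The case against.** **Direction.** A reader might infer that the gap favours the drug. The protocol does not support that. Section 3.1 says these lesions generally worsen if untreated, and 8.6.2.1 expects no natural improvement. Regrowth after the herbal medicine is stopped would enlarge the lesion before dosing and work against a 20% reduction. Only continued shrinkage after the MRI inflates response. This objection stands.

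**Size.** The 46 and 106 days are corner cases, and the number of users and the strength of any effect are unknown. This stands too. It is also tempting to say that one wrongly credited responder reverses the result at 8 of 19 or 9 of 22. That is true of any misclassification in any exact binomial test, and it matters only if the count lands on the boundary. It adds nothing about herbal medicine.

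**No limit on MRI age.** Footnotes 8 and 10, if read as meaning the first consent, might seem to leave the age of the MRI at dosing unbounded. That reading is strained. The sentence concerns consent being obtained again, and 6.2.1 names re-consent as the reference date. Read together, the limit is 90 days before re-consent. What remains is a wording mismatch.

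**Existing safeguards.** Criterion 2 excludes current users and eligibility is settled at screening, so one may argue that the drug must already have been stopped by then. But the exception counts from dosing, which permits a later stop. Even if the stop had to come by consent, an MRI 30 days before consent would leave up to 30 days of exposure after it. Recording from consent, the investigator's discretion under criterion 12 and the case review in 8.1.3 make most post-consent exposure visible. They do not cover use before consent, and none of them ties the baseline image to the stop.

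**Conclusion.** The concern holds as a gap in timing. By the protocol's own windows, an eligible subject can be exposed for up to 46 days after the baseline image, or 106 days after re-consent, to a medicine that the protocol itself says may influence the lesion. The single-arm design attributes any resulting change to the study drug.

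The protocol does not support a claim that the result will be biased, in which direction, or by how much. That depends on how many subjects use herbal medicine around their baseline MRI and on what it does to lesion volume; neither is given. The conclusion rests on the stated windows and on the re-consent restarting the 30-day dosing window. Only herbal users are affected, and the planned sample size, alpha and power are unchanged. The point is worth correcting because it is a stated rule, the correction is cheap, and unrecorded exposure before consent cannot be recovered at analysis.

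**What to change.** Reconcile criterion 2 (synopsis and 3.2.2.2), section 4.2.1, section 6.2.1 and the two table footnotes so that the herbal stop and the baseline volume share one anchor. Specifically:

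1. For herbal-medicine users, do not adopt as the pre-administration image any MRI taken before the discontinuation that criterion 2 requires. Time the scheduled screening MRI after that discontinuation.
2. Record herbal use from the date of the adopted baseline MRI where that is earlier than consent, so that exposure in the interval can be identified.
3. Align footnote 8 to Table 6.1.1-1 and footnote 10 to Table 6.1.2-1 with the re-consent wording in 6.2.1.

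The length of the washout is a clinical matter for the sponsor. With the baseline image taken after the stop and no resumption before dosing, permitted exposure after that image falls to 0 days. A withdrawal effect that continues after the image could remain; how far it does depends on the washout length.

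The cost is a few lines of text and one extended recording period. For herbal users only, an earlier clinical MRI could not be reused and the timing of the screening MRI would be constrained.
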